### Aims

This study specifically set out to investigate the effectiveness of Falloon and co-workers’ Psychoeducation Program (FPP) and to evaluate its feasibility as part of the standard care setting provided by the INHS. The FPP will be compared to a control group, and randomized to a treatment with generic information on the disorders administered with the same frequencies as the FPP (Generic Treatment (GT)). We foresee that the FPP will be effective in improving adherence to pharmacotherapy in the exposed group when compared to the non-exposed group, and we also expect that the FPP will reduce the risk of relapse and readmission in the exposed group, by maintaining its effects at both six-and twelve-month follow-ups. Positive results would imply the importance of applying the FPP in all INHS settings, and the need of exploring its potential in other classes of psychosis, such as affective psychoses, which are also burdened by high personal, family and social costs.

A secondary goal of the study is the production of a manual to be used in the training and assessment of the professional staff involved in the treatment of patients diagnosed with schizophrenia-spectrum psychosis.

The primary outcome of the study, adherence to therapy, will be measured through a triple approach: a scaled self-report questionnaire, a four-query interview and, for the first time, the blood levels of the primary prescribed drug (to be measured by a specialized pharmacology unit with extensive experience in this type of studies). In this way, we will be able to validate the simpler instruments of measurement, such as the self-report or interview, with an objective, gold-standard method (blood levels of the therapeutic compound), a practice rarely used in past studies on adherence to therapy in patients with psychosis [27]. If one or both of the simpler, self-report instruments of assessment prove to be valid enough to differentiate adherent from non-adherent or partially adherent patients, the study will produce add-on information on easy-to-be-administered tools, to be generalized for future related studies.

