### Assessment and outcome measures

Assessment is aimed at investigating the clinical and functional status of the patients and evaluating the main effects of treatment on the primary and secondary outcome measures (Table 3). The primary outcome is the patient’s adherence to pharmacotherapy, intended as the continuous use of the primary prescribed drug. Even if patients with psychosis are generally under poly-pharmacotherapy, only adherence to the most important drug (the one expected to produce the main therapeutic effect), as indicated by the enrolling unit, will be monitored during the study. Adherence will be checked by a triple method of assessment: patient’s self-report on the Medication Adherence Rating Scale (MARS), patient’s replies to the four-query interview of the Brief Adherence Rating Scale (BARS), and measurement of blood levels of the prescribed drug. Data will be analyzed using two indicators of adherence:

1. a dichotomic index, where non-adherence is the lack of adherence to the treatment in 30% or more of the monthly evaluation on the self-report or the interview (since replies on both measures might not coincide);

2. a continuous index based on the scale - self-report or interview - which could be the most reliable by comparison with the measurement of blood levels of the primary prescribed drug, to apply statistical analyses of covariance and verify the impact of confounding variables on the primary outcome.

**Table 3 T3:** Timing of assessments of endpoints for efficacy and safety

	**T0**	**T1**	**T2**	**T3**
Background information (age, sex, diagnosis, and so on)	X			
Clinical Global Impressions	X	X	X	X
Brief Psychiatric Rating Scale (BPRS)	X	X	X	X
Positive And Negative Syndrome Scale (PANSS)	X	X	X	X
Social Performance Scale	X	X	X	X
Health of the Nation Outcome Scales (HoNOS)	X	X	X	X
World Health Organization Quality Of Life (WHOQoL)	X	X	X	X
The Family Questionnaire	X	X	X	X
Medication Adherence Rating Scale	X	X	X	X
Brief Adherence Rating Scale	X	X	X	X
Dosage Record and Treatment Emergent Symptoms Scale (DOTES)	X	X	X	X
Sheenan-Suicidality Tracking Scale (S-STS)	X	X	X	X
Modified Overt Aggression Scale (MOAS) 1.0	X	X	X	X
Blood sample for assessing of the blood level of the prescribed drug	X	X	X	X
Assessment of blinding				X

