### Follow-up assessment

The FPP has a six-month duration, so patients will be assessed at entry (t0), at the end of the FPP (t1), at the six-month follow-up (t2), and at the twelve-month follow-up (t3), for secondary outcome measures. Adherence will be monitored at t0, t1, t2, and t3, via self-reports, interviews and measured blood levels of the primary prescribed drug.

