### Data management and analysis

All analyses will be based, as far as possible, on the intention-to-treat principle. Differences in the primary outcome (adherence to pharmacotherapy) will be analyzed with a two-tail test for proportions with the Miettinen exact test [61]. A multiple logistic regression will be carried out to control for the confounding variables [62] using adherence (yes/no) as the outcome to verify the impact of the FPP on controlling the impact of the confounding variables (sex, age, severity of the disorder, cluster).

Survival analyses will be performed using the Kaplan-Meier method, followed by the log-rank test to define the terminal events at both the start of non-adherence and the first relapse or readmission episode [63]. Intention-to-treat will be applied considering the primary and secondary outcomes [64]. Multiple imputations will be applied to integrate missing data [65].

As far as validation of the self-report (MARS) and the interview (BARS) measure of adherence with respect to the blood levels of the main prescribed drug is concerned, Spearman’s rho will be used to compare blood levels of the main drug with the self-report or the interview; partial correlation will be used to ascertain the links between blood levels of the main drug with the self-report or the interview by taking into account the other measures (the interview or the self-report, respectively).

All analyses will be done with Excel (Microsoft Excel 2013 running on Windows 8) (Chicago, IL 60606, USA) or the Statistical Package for Social Science (SPSS) version 17 for Windows.

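### MARS and BARS are to be validated as classifiers of adherence, but only correlations with blood level are planned, and the choice of the continuous adherence index is not confined to pre-treatment data

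*Protocol article*

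**What the plan says.** The Protocol article's Aims section sets the validation question: whether one or both of the simpler instruments "prove to be valid enough to differentiate adherent from non-adherent or partially adherent patients". The comparison is to be made "with an objective, gold-standard method (blood levels of the therapeutic compound"). If it succeeds, the tools are to be offered for use in later studies.

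The section Data management and analysis gives the method. Spearman's "rho will be used to compare blood levels of the main drug with the self-report or the interview", and "partial correlation will be used to ascertain the links between blood levels of the main drug with the self-report or the interview", each scale being adjusted for the other. No other validation analysis is described.

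The section Assessment and outcome measures defines two adherence indicators. The dichotomous one is a rule "where non-adherence is the lack of adherence to the treatment in 30% or more of the monthly evaluation on the self-report or the interview"; it uses both scales and involves no selection. The continuous one is a single scale, self-report or interview, "which could be the most reliable by comparison with the measurement of blood levels of the primary prescribed drug", and it is meant for analyses of covariance and confounding.

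On timing, the section Follow-up assessment says: "Adherence will be monitored at t0, t1, t2, and t3, via self-reports, interviews and measured blood levels of the primary prescribed drug". The Medication section places no restriction on drug treatment.

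**The concern.** Telling adherent patients from the others is a classification task. Rank correlation and partial correlation measure how strongly two quantities move together. They do not say how many non-adherent patients a scale would find, how many adherent patients it would mislabel, or where to cut it. The protocol states a method, and that method answers a different question from the one in the Aims. A later study adopting MARS or BARS in place of blood sampling would not learn from rho how often the scale misclassifies.

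The second strand concerns the continuous index. One of the adherence outcomes is to be settled by a comparison within the study's own data, and nothing limits that comparison to baseline. Table 2 gives both arms a session on drugs (FPP week 5, GT week 4) and gives GT a session on therapy acceptance (week 11). After t0, reporting could therefore shift without intake shifting, and not necessarily equally in the two arms. A scale chosen on such data would be chosen partly on what treatment did to it.

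**Working it through.** The protocol states no target correlation, sensitivity, specificity or sample size for the validation, so there is no figure to reproduce. The check is of what a correlation can and cannot show.

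**1. Aim against method.** The Aims call for separating groups of patients. The analysis section offers rho and partial correlation against the blood level. It gives no blood-level class, scale cut-off, sensitivity, specificity or ROC analysis. The partial correlation is also a measure of association, so it does not close the gap.

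**2. What a given correlation means for classification.** The 47% non-adherence comes from Sample size and power. Assumed: bivariate normality, both measures cut at 47%, and the correlations shown. With c the 47th normal percentile and J = Φ₂(c, c; r):
- sensitivity = J / 0.47
- specificity = (1 − 2 × 0.47 + J) / 0.53
- r = 0.4: J = 0.286, so sensitivity 0.286/0.47 = 61% and specificity (0.06 + 0.286)/0.53 = 65%
- r = 0.6: J = 0.323, so sensitivity 69% and specificity (0.06 + 0.323)/0.53 = 72%

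Converting Spearman to Pearson moves these by less than one percentage point. MARS runs only from 0 to 5, so normality is a rough approximation.

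**3. Same rho, different accuracy.** In this simulation every input except the 47% is assumed. True intake is uniform on 0–70% in non-adherent and 70–100% in adherent patients. Blood level is intake times log-normal variability (log-SD 0.4). The scale hides a share b of missed doses, has noise SD 0.1(1 − b), and is cut at 70%. There were 20 runs of 20,000 patients on a single drug.

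| b | rho | sensitivity | specificity | ROC area |
|---|---|---|---|---|
| 0 | 0.73 | 0.94 | 0.87 | 0.98 |
| 0.3 | 0.73 | 0.81 | 0.98 | 0.98 |
| 0.6 | 0.73 | 0.36 | 1.00 | 0.98 |
| 0.8 | 0.73 | 0.00 | 1.00 | 0.98 |

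Over-reporting of this kind is nearly a monotone change of the scale, so a rank statistic cannot see it. The ROC area cannot see it either. Only sensitivity and specificity at a stated cut-off reveal it.

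**4. Different rho, same accuracy.** With eight drugs of differing level (log-SD 1.5) and dose (log-SD 0.4), mean rho falls to 0.37 (range 0.29 to 0.52). Sensitivity, specificity and ROC area for true adherence stay as in the table. The Medication section says drug type and dose will be controlled as potential confounders, but does not tie this to the blood-level correlation.

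**5. Choice of the continuous index.** The text requires comparison with blood levels and names no statistic, visit or rule for a tie. Table 3 schedules MARS, BARS and blood at t0, t1, t2 and t3, so baseline data for the choice will exist.

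**The case against.** The article condenses a fuller plan, and the visit or pooling rule for a sub-analysis is commonly left to the SAP. That stands: the visits are listed, and an unnamed visit alone would be no finding. It does not cover the mismatch of aim and method, because there the article states the method.

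Several stronger readings are tempting but not supported:

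- A reader might infer that any significant rho would count as validation. With 340 pairs that is a rho of about 0.106. No section makes significance the criterion, and 340 complete pairs are unlikely because Potential limitations foresees drop-out and refusal of blood sampling.
- A reader might infer that the continuous index is chosen by rho. The text says only that it is chosen by comparison with blood levels. Rho and partial correlation are the only such comparisons described, but the link is an inference.
- A reader might infer that choosing between two scales inflates the trial's false-positive rate. That would need the choice to be steered by arm differences. The stated basis is agreement with blood level, and Ethical considerations says the statistical units receive groups coded A and B. The primary test is of proportions, which fits the dichotomous index, where nothing is selected.

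It is also fair to say that the simulated fall in sensitivity comes from holding the cut-off fixed, and that ROC area is as blind to it as rho. This argues for reporting accuracy at a stated cut-off, not for correlation alone. Finally, the Aims call the validation add-on information, so the stakes are modest.

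**Conclusion.** The concern holds in a limited form. The stated validation aim is discrimination and the stated analyses are correlations, so carrying them out as written would not answer the question. This rests on the text alone. The figures (69% sensitivity and 72% specificity at a correlation of 0.6; unchanged rho with sensitivity from 0.94 to 0.00) illustrate the gap on assumed inputs and are not estimates for this trial.

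The choice of the continuous index is a lesser weakness: it is made to depend on study data without being confined to pre-treatment data. That sessions change reporting without changing intake is possible from Table 2 but is not shown. The consequence is limited to the continuous covariance analyses. Nothing here undermines the primary comparison of proportions or its error rate. The point is an inexpensive improvement, not a threat to the main conclusion.

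**What to change.** 1. **Validation aim.** Define the blood-level adherence class so that it is standardised for drug and prescribed dose and can represent partial adherence. A simple split into drug detected or not detected would not do the latter. For MARS and BARS separately, report sensitivity, specificity and ROC area with confidence intervals. Set the scale cut-off in advance; if it is derived from the same data, correct the accuracy for optimism, for example by bootstrap. Keep rho and the partial correlation as descriptive results.

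2. **Continuous index.** Choose the scale once, from t0 data, by a named criterion such as the larger ROC area against the blood-level class. Fix the choice before follow-up data are compared by arm.

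The cost is some plan wording and added analysis on samples and scales already scheduled in Table 3. The downside is fewer pairs for the choice: at most 340 at t0, against at most 4 × 340 = 1,360 repeated pairs over all four visits, before drop-out and refusals.

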### Ethical considerations

The FPP is not expected to produce relevant somatic side effects but it can produce unwanted or unforeseen effects, such as an increase in the intra-family level of conflict. To maximize safety for the patients, before randomization each patient will be evaluated on his or her risk of unwanted or unforeseen effects attributable to exposure to the FPP.

The therapists involved in the administration of the FPP and GT will be monitored to minimize any improper method of administration of the protocol of treatment; assessors will also be trained and monitored to avoid dispersion of information, thus violating the guaranteed criterion of good faith in case of patients’ disclosing sensitive information. Data recording and storage will comply with the privacy law in force, and informed consent for information recording will be obtained from each patient.

Participation in the study is voluntary and written informed consent is obtained. Before enrollment, participants will receive both verbal and written assurance that they can withdraw from the trial any time, with no consequence for their continued treatment. Patients unable to give informed consent in an appropriate way or who refuse to participate in the study will not be enrolled.

The Training Center is committed to monitoring the quality of assessment and of the administration of the FPP procedures, on a three-month basis.

A paradoxical, unintended effect of greater adherence to pharmacotherapy is the potential increase of the somatic side effects of the prescribed drugs. Indeed, there is some indirect evidence that this can actually occur [66]. To limit this paradoxical effect, patients will be closely monitored for side effects and somatic conditions on a three-month basis or as needed. It is expected that, following improvement in the response to the therapy as a result of greater adherence to pharmacotherapy, the therapist will decrease dosage of the prescribed drugs. This specific change will be checked at assessment and a reduction of dosage of the prescribed drugs and of poly-pharmacotherapy is among the secondary outcomes of the study.

Regarding the obligation to professional secrecy, this is the responsibility of the enrolling unit, and all data are recorded anonymously and coded with a concealed script, which will not be disclosed until the end of the study. Only the Coordination Center owns these concealed codes, not to be disclosed to the statistical units, which will receive the data with a neutral assignment (group A, group B).

### Safety

Safety will be closely monitored. Key endpoints will be:

•death caused by suicide

•suicide attempt

•suicidal crisis (explicit plan for serious suicidal activity without suicide attempt)

•severe symptomatic exacerbation, defined by the Clinical Global Impression Scale (CGI), which includes ratings of illness severity and changes in overall clinical status. A rating of CGI-severity ≥ 6 (severely ill) and CGI-change ≥ 3 (much worse) would be regarded as severe symptomatic exacerbation.

Information about these safety variables is recorded in the Case Report Form (CRF) as part of the regular clinical assessment.

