The CGI is a tripartite rating scale aimed at assessing the severity of the patient at the moment of the assessment, improvement or worsening relative to the baseline, and efficacy of treatment (described in [34]). The CGI-severity rating is provided on a seven-point scale that assesses severity of the patient on the basis of total clinical impression: 1) not at all ill; 2) borderline mentally ill; 3) mildly ill; 4) moderately ill; 5) markedly ill; 6) severely ill; or 7) extremely ill. The CGI-change is provided on a seven-point scale, rated as: 1) very much improved; 2) much improved; 3) minimally improved; 4) no change; 5) minimally worse; 6) much worse; or 7) very much worse. The CGI-efficacy index is a rating scale crossing the efficacy of the treatment by occurrence of side effects: 1) unchanged to worse; 2) minimal efficacy; 3) moderate efficacy; 4) marked efficacy, with side effects rated as: 1) none; 2) does not interfere with patient’s functioning; 3) interferes with patient’s functioning; 4) outweighs therapeutic effects. A higher score on the CGI-severity and the CGI-change rating corresponds to greater severity and worsening, respectively. Conversely, a higher score on the CGI-efficacy index corresponds to better efficacy (however, greater side effects counterbalance efficacy).

The BPRS is a 24-item measure of general psychopathology in a Likert format, with scores from 1 (absent) to 7 (extremely severe) [35,36]. Possible BPRS total scores varied from 24 to 168. The primary purpose of the BPRS is to allow assessment of treatment change across a comprehensive set of common symptom characteristics. The original 16-item BPRS was initially expanded to 18 items, then to 24 items by adding 6 symptom items (bizarre behavior, self-neglect, suicidality, elevated mood, distractibility, and motor hyperactivity) to increase sensitivity to a broader range of psychotic and affective symptoms [37]. A higher score on the BPRS corresponds to greater psychopathology.

The PANSS is a measure of the current symptoms of patients on a 30-item scale [38,39]. The PANSS consists of three domains: positive symptoms, negative symptoms, and general psychopathology. Items are rated from 1 (absent) to 7 (extremely severe); the total score varies from 30 to 210. A higher score on the PANSS corresponds to greater psychopathology.

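### The CGI-change cut-off for severe symptomatic exacerbation contradicts its own label: read literally, patients at CGI-severity 6 or 7 who are unchanged or minimally improved also qualify

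*Protocol article*

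**What the plan says.** The Safety section names four key endpoints: death by suicide, suicide attempt, suicidal crisis, and "severe symptomatic exacerbation, defined by the Clinical Global Impression Scale (CGI"). The last has two conditions that must hold together: "A rating of CGI-severity ≥ 6 (severely ill) and CGI-change ≥ 3 (much worse"). The change condition and its consequence read: "CGI-change ≥ 3 (much worse) would be regarded as severe symptomatic exacerbation".

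The scale itself is set out under Assessment tools. CGI-change rates "improvement or worsening relative to the baseline" on seven points: "1) very much improved; 2) much improved; 3) minimally improved; 4) no change; 5) minimally worse; 6) much worse; or 7) very much worse". The upper end of the severity scale reads "5) markedly ill; 6) severely ill; or 7) extremely ill". The direction of both scales is explicit: "A higher score on the CGI-severity and the CGI-change rating corresponds to greater severity and worsening, respectively".

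Table 3 schedules the CGI at T0, T1, T2 and T3. The eligibility criteria (text and Table 1) set no limit on CGI-severity at entry.

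**The concern.** The Safety section attaches the words much worse to a score of 3. Assessment tools places 3 on the improvement side of the scale and gives much worse the score 6. In the same sentence the severity cut-off does match its label (6 is severely ill), so the mismatch is confined to the change criterion.

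The change criterion is what separates a patient who has deteriorated from one who was already severely ill. At a cut-off of 3 it removes only patients who are much or very much improved. A patient who enters at CGI-severity 6, stays at 6 and is rated no change at T1, T2 and T3 would meet the definition at each of those visits.

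This matters because the Ethical considerations section says the programme could have unwanted effects, such as more conflict within the family. Of the four key safety endpoints, this is the only one that measures symptomatic worsening. If stable severe illness is mixed into it, it becomes less specific for the harm it is meant to detect. Ten enrolling units or a programmer could also resolve the conflict in different ways, some following the number and others the words.

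**Working it through.** No sample-size or power figure is involved. The check is a look-up followed by a count of scale cells.

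**Inputs**
- Safety: severity at least 6 (labelled severely ill) and change at least 3 (labelled much worse).
- Assessment tools: seven change anchors and seven severity anchors, with higher scores meaning worse on both.

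**Step 1: do the labels match the scores?**

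| Criterion | Cut-off in Safety | Label in Safety | Anchor at that score in Assessment tools | Match |
|---|---|---|---|---|
| CGI-severity | 6 | severely ill | severely ill | yes |
| CGI-change | 3 | much worse | minimally improved | no |

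The pairing of 3 with much worse cannot be reproduced from the protocol's own scale.

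**Step 2: could another coding rescue it?** The article gives no other coding of CGI-change. Two obvious transformations were tried.
- Centred on no change (score − 4): much worse is 6 − 4 = +2, and +3 is very much worse (7 − 4).
- Reversed (8 − score): much worse is 8 − 6 = 2, and 3 is minimally worse (8 − 5). A rule of at least 3 would then leave out much worse. The stated direction of the scale rules out reversal in any case.

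Under neither transformation does 3 mean much worse.

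**Step 3: what does the literal rule admit?** Severity 6 to 7 gives 2 levels and change 3 to 7 gives 5 levels, so 2 × 5 = 10 qualifying score pairs.

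| CGI-change | Anchor | Pairs (severity 6 and 7) |
|---|---|---|
| 3 | minimally improved | 2 |
| 4 | no change | 2 |
| 5 | minimally worse | 2 |
| 6 | much worse | 2 |
| 7 | very much worse | 2 |

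- Pairs with no worsening (change 3 or 4): 2 + 2 = 4 of 10.
- Pairs short of the label (change 3, 4 or 5): 2 + 2 + 2 = 6 of 10.
- Pairs at or beyond the label (change 6 or 7): 2 + 2 = 4 of 10.

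**Step 4: what if the label governs?** Severity 6 to 7 with change 6 to 7 gives 2 × 2 = 4 pairs, none of them unchanged or improved. All four are among the 10 in Step 3, so the literal rule adds pairs to the label's set and loses none.

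**The case against.** The best defence is that the intent is easy to see. The endpoint is called an exacerbation and the criterion is worded as worsening, so a slip in the number is the likeliest explanation and a clinician would probably follow the words. The other three key safety endpoints do not use the CGI. The article ties no stopping rule to this endpoint, and neither the primary adherence outcome nor the sample size depends on it. CGI scores are collected at every assessment, so the endpoint can be re-derived without new data. The CRF and the full protocol are not shown and may carry a consistent definition.

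Most of this stands, and it limits the consequences. It does not remove the contradiction: a derivation works from the number, and nothing else in the article says whether the number or the label prevails.

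Four stronger readings are tempting but not supported:
- A reader might infer that unchanged and improving patients in general are counted. The rule is joint, so only those at CGI-severity 6 or 7 are affected, and scores 1 and 2 are excluded, so improvement here means minimal improvement only.
- A reader might infer that the endpoint would consist largely of stable patients. The article gives no CGI distribution, and even among scale cells only 4 of 10 show no worsening.
- A reader might infer that real worsening would be missed. The literal rule is over-inclusive, so every patient who meets the label still qualifies. The harm is dilution by false positives.
- A reader might infer a bias towards one arm. Nothing in the article shows a differential effect. Allocation is 1:1 and stratified by site, and over-counting would occur in both arms.

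**Conclusion.** The point holds. A key safety endpoint has a threshold that contradicts its own label on the protocol's own scale, and no other section resolves it. On the literal reading, 6 of the 10 qualifying score pairs fall short of the label and 4 of the 10 show no worsening. The endpoint could therefore include severely ill patients who are stable or slightly better, which would dilute true worsening.

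This rests on the scale in Assessment tools being the one the raters use, which is the only version the article gives. How many patients or events are affected cannot be computed from the document. The document also does not settle which of the two was intended, the number or the label.

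**What to change.** Before safety data are tabulated, the sponsor should state which was intended and make the number and label in Safety agree with the CGI-change anchors in Assessment tools. The same definition should be used in the CRF derivation and given to all enrolling units. If any events have been coded with the cut-off of 3, they should be re-derived under the reconciled definition.

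The cost is a one-line correction, plus, where needed, a re-derivation from CGI scores already collected. No new assessments are required, and the sample size and the primary analysis are unaffected.
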